### Sample size

2.12

Enrolment estimates are derived from SHRiSTI ASHA pregnancy surveillance data which indicates a mean of 4.6 stillbirths per block per month (range: 3.4–5.6), with a seasonal peak during July–October (5.2–5.6 per block per month) *(surveyed data from SHRiSTI project)*. This pattern is consistent with published systematic review by Lakhoo et al. on heat-associated stillbirth risk in South Asian settings in 2025. As described in Section 2.1, the SHRiSTI community-based surveillance estimate of 17.2 per 1,000 total births is used for planning, as it more accurately captures the true community-level burden than the HMIS facility-based figure.. The per-block estimate from the same surveillance data is 4.6 per month and this was used as a base for sample size. The study will employ a difference-in-differences (DiD) design across four blocks (two intervention, two control). With two blocks per arm, the expected enrolment rate is approximately 9.2 women per arm per month. Over the 8-week pre-intervention period, approximately 17 women per arm are expected, and over the 26-week post-intervention period, approximately 56 women per arm are expected, yielding a total sample of approximately 146 women.

The primary outcome is mean EPDS score (continuous). Assuming a clinically meaningful difference of 3.5 points, a pooled standard deviation of 6.5, two-sided alpha of 0.05, and 80% power, a minimum of 55 women per arm in the post-intervention period is required. The expected sample size of 56 per arm provides approximately 81% power. To account for an anticipated 10% attrition rate, the post-intervention data collection period may be extended to ensure a minimum effective sample size of 56 women per arm.

A pre-specified sensitivity analysis including early neonatal deaths (<24 h) is expected to add approximately 18 cases per arm. This estimate is based on a neonatal mortality rate of ∼22 per 1,000 live births in Haryana, with approximately 25% of deaths occurring within 24 h, applied to an estimated 277 live births per block per month. This yields approximately 1.5 early neonatal deaths per block per month, resulting in ∼18 additional cases per arm over the study period. The resulting post-intervention sample of approximately 74 per arm would provide approximately 91% power.

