### Statistical analysis

2.13

The primary Difference-in-Differences (DiD) model will be specified as a linear regression with block fixed effects:$$EPDS=\beta_{0}+\beta_{1}(Arm)+\beta_{2}(Time)+\beta_{3}(Arm\times Time)+\gamma_{k}(Block_{k})+\epsilon$$where *Arm* (1 = intervention, 0 = control), *Time* (1 = post, 0 = pre), and the interaction term (*Arm* × *Time*) represents the DiD estimator (*β*₃). A negative *β*₃ will indicate a reduction in depressive symptoms attributable to C-COMPASS. Block fixed effects (*γ*_k_) will account for time-invariant block-level confounders, including baseline ASHA performance, population characteristics, and facility access.

The pre-specified secondary binary outcome (EPDS ≥ 13) will be analysed using a logistic DiD model with the same structure. SDS and BGQ scores will be analysed using linear DiD models with block fixed effects, while BGQ screen-positive (≥4) will be analysed using logistic DiD models. Implementation outcomes (visit completion, referral completion, and documentation completeness) will be reported as proportions with 95% confidence intervals.

Parallel trends will be assessed by comparing pre-intervention EPDS distributions across study arms and blocks, along with baseline sociodemographic characteristics (20). A maximum of one additional covariate beyond block fixed effects will be included, selected *a priori* (most likely gravida or previous stillbirth) (21). A pre-specified sensitivity analysis will replicate the primary model in an expanded population including early neonatal deaths, incorporating a perinatal loss type indicator and its interaction with the intervention effect. All analyses will be conducted using Stata version 16 or R version 4.4+.

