
### Policy implications and future research

3.2

This study is designed from the outset to generate evidence that is actionable within India's government health system. The outcome measures, mean EPDS score, 72 h visit coverage rate, three-visit completion, referral completion, align directly with NHM programme monitoring indicators. The documentation pathway, a C-COMPASS column in the existing ASHA register, requires no new technology and no new reporting layer. The Tele-MANAS referral is already national infrastructure. If C-COMPASS achieves feasibility (≥70% 72 h coverage) and demonstrates a clinically meaningful reduction in mean EPDS score, the findings will be presented to the Haryana State Health Mission with a costed phased scale-up plan covering all six Palwal blocks, and subsequently to the national NHM technical advisory group for maternal mental health. The incremental cost analysis will provide the economic argument: if C-COMPASS can be delivered at a per-woman cost comparable to other NHM community interventions, the case for national integration becomes substantially stronger. The pre-specified sensitivity analysis for early neonatal deaths addresses the policy question of whether a single protocol can serve the full perinatal mortality framework population, if the answer is yes, the scope of the programme and its potential impact more than doubles without requiring protocol redesign. Future research priorities include a fully powered cluster-randomised controlled trial with the administrative block as the unit of allocation and a pre-specified intra-cluster correlation coefficient; longitudinal follow-up at 6 and 12 months to assess persistence of effects on grief and functional recovery; a formal health economic evaluation incorporating DALY metrics and multi-year programme costs; and deliberate protocol adaptation studies for early neonatal death, late miscarriage, and preterm birth with subsequent infant death, each requiring their own co-design process and piloting before evaluation. Also, systematic reviews and meta-analysis to generate evidence on effective interventions for promoting mental health in the reproductive continuum must be undertaken (28). The implementation science approaches applied in C-COMPASS, including quasi-experimental design for programme evaluation, mixed-methods feasibility assessment, and health systems integration, build on methodological frameworks previously applied to community-based child health programme implementation in comparable North Indian settings, where structured implementation research has demonstrated the value of embedding evaluations within existing health system infrastructure to generate actionable evidence for national programme scale-up (29, 30, 31).

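### The 91% power stated for the early-neonatal-death sensitivity analysis belongs to a pooled post-period comparison, not to the planned difference-in-differences model with a loss-type interaction, whose power is about 10% to 35%

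*Protocol article*

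**What the plan says.** Section 2.12 (Sample size) sets the planning values for the primary outcome: "Assuming a clinically meaningful difference of 3.5 points, a pooled standard deviation of 6.5, two-sided alpha of 0.05, and 80% power". It arrives at 55 women per arm and adds: "The expected sample size of 56 per arm provides approximately 81% power". For the expanded population it states: "A pre-specified sensitivity analysis including early neonatal deaths (<24 h) is expected to add approximately 18 cases per arm". This gives 56 + 18 = 74 per arm after the intervention starts, and then: "The resulting post-intervention sample of approximately 74 per arm would provide approximately 91% power". The sentence does not name the test to which the 91% refers.

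Section 2.13 (Statistical analysis) says the sensitivity analysis repeats the primary DiD model in the expanded population, "incorporating a perinatal loss type indicator and its interaction with the intervention effect". The related secondary objective (section 2.3.1.2) is exploratory: do effects stay consistent once early neonatal deaths within 24 h are added to stillbirths?

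Section 3.2 (Policy implications and future research) presents this analysis as addressing whether a single protocol can serve all perinatal losses, and continues: "if the answer is yes, the scope of the programme and its potential impact more than doubles without requiring protocol redesign". The article gives no power or precision for the interaction and no rule for what would count as a yes.

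**The concern.** The stated power and the planned analysis do not match, in two respects. The 91% uses post-period women only, whereas the planned estimator also subtracts a pre-period difference measured in few women. It also treats all 74 women per arm as one group. Once a loss-type interaction is in the model, the Arm × Time coefficient is the effect in the reference loss type and the interaction is the difference between loss types. Neither is the contrast that has 91% power.

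Of the 74 women per arm, 56 are the stillbirth women of the primary analysis, so a pooled result mostly restates the primary result. What the analysis can add is information on about 18 early neonatal deaths per arm. The 91% says nothing about how well the effect in those women, or its difference from the effect after stillbirth, will be known. Section 3.2 attaches a programme-wide statement to that question. The protocol itself gives a reason to expect a difference: section 2.5.1 says the counselling narrative needs adapting for women who briefly held a live-born baby.

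**Working it through.** **Inputs.** From section 2.12: difference 3.5, SD 6.5, two-sided alpha 0.05. Per arm there are 56 stillbirths post-intervention, 17 stillbirths pre-intervention ("Over the 8-week pre-intervention period, approximately 17 women per arm are expected"), and 18 added early neonatal deaths. The 18 equals 1.5 per block per month × 2 blocks × 6 months, so it is taken as a post-period count.

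**Assumed.** The protocol gives no pre-period count of early neonatal deaths. At the same rate, 1.5 × 2 × 8 weeks ÷ 4.345 weeks per month ≈ 5.5 per arm. Women are treated as independent, the SD is equal across loss types and periods, and there is no attrition.

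Power is Φ(difference/SE − 1.96) throughout.

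**1. The plan's own figures.**
- 56 per arm: SE = 6.5 × √(2/56) = 1.228; power = 81.3% (stated 81%).
- 74 per arm: SE = 6.5 × √(2/74) = 1.069; power = 90.6% (stated 91%).

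Both reproduce as post-period two-sample comparisons. The arithmetic is right for that test.

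**2. Pooled effect in DiD form.** Pre-period 17 + 5.5 = 22.5 per arm.
- SE = 6.5 × √(2/74 + 2/22.5) = 2.21.
- Power for 3.5 points = Φ(1.58 − 1.96) ≈ 35%.

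**3. Difference between loss types.** The target is 3.5 points: full effect after stillbirth, none after early neonatal death. Section 2.13 does not fix the lower-order terms, so three forms are shown.

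| Form | SE | 95% CI half-width | Power |
|---|---|---|---|
| Minimal model: loss indicator plus loss × Arm × Time only | 2.24 | 4.4 | about 35% |
| Post-period only | 2.49 | 4.9 | 29% |
| Full DiD interaction with all lower-order terms | 5.15 | 10.1 | about 10% |

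- Minimal model: each arm-by-period cell contributes information n₁n₂/(n₁ + n₂) on the loss-type difference. This is 56 × 18/74 = 13.62 in each post cell and 17 × 5.5/22.5 = 4.16 in each pre cell. SE = 6.5 × √[1/13.62 + 1/(13.62 + 2 × 4.16)] = 2.24. This form assumes that, without the intervention, the loss-type difference in EPDS is the same in both arms and both periods.
- Post-period only: SE = 6.5 × √(2/56 + 2/18) = 2.49.
- Full DiD interaction: SE = 6.5 × √(2/56 + 2/18 + 2/17 + 2/5.5) = 5.15.

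Every half-width exceeds 3.5. If there were no benefit after early neonatal death, the interaction would be non-significant in about 65% (minimal), 71% (post-only) or 90% (full DiD) of studies.

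**4. Effect in early neonatal deaths alone, post-period only.** SE = 6.5 × √(2/18) = 2.17; half-width 4.2; power about 37%.

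**5. Sensitivity to the assumptions.**
- The abstract and section 2.4 give a pre-period of about 10–12 weeks instead of 8. With 21 to 25 stillbirths and 7 to 8.3 early neonatal deaths per arm, pooled DiD power is about 40% to 45%, the full interaction about 11% to 12%, and the minimal model about 36%.
- If the 18 deaths cover all 34 weeks (26 + 8), about 13.8 per arm fall post-intervention. Post-only power drops to about 24% and the full interaction to about 9%.

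**The case against.** **The figure is arithmetically correct and tied to a post-intervention sample of 74.** Both are true. The fault is that it is the only power figure given for an analysis whose model is different.

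**The objective is exploratory and concerns an expanded population, and low interaction power is usual for an added subgroup.** This stands and limits the weight of the point. However, section 2.13 itself includes the interaction, and section 3.2 itself draws on the analysis for a policy question. For the binary EPDS outcome, section 2.12 discloses 44% power, calls the analysis exploratory and commits to confidence intervals. The loss-type analysis has lower power but carries a reassuring figure.

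**The policy stake is limited.** Largely fair. In section 3.2, scale-up depends on 72 h coverage and the EPDS reduction, and adaptation studies for early neonatal death appear there as future research. The statement about more than doubling scope is conditional, but it still rests on this analysis.

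**Stronger readings that the document does not support.**
- A reader might infer that 29% is the best attainable power, or 4.9 points the narrowest half-width. The minimal reading of section 2.13 gives about 35% and 4.4, and a loss-type difference larger than 3.5 points would have more power.
- A reader might infer that a yes is close to automatic. No rule equates a non-significant interaction, or a similar pooled estimate, with a yes. Non-significance under no benefit is likely (65% to 90%), not certain.
- A reader might infer that the pooled test would remain significant about 70% of the time with no effect after early neonatal death. In that case the pooled effect is 3.5 × 56/74 = 2.65, and 70% is its power in the post-only test, which is not the planned one. In DiD form it is Φ(2.65/2.21 − 1.96), about 22%.

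**Conclusion.** The point holds as a mismatch between a stated power and the analysis to which it is attached. The 91% is pooled, post-only power. No coefficient of the planned model has it: the pooled DiD effect has about 35%, and a 3.5-point loss-type difference about 10% to 35% depending on which interaction terms are fitted. With half-widths of about 4.4 to 10 EPDS points, the analysis is unlikely to separate full benefit from none after early neonatal death.

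These figures rest on the protocol's SD and counts, on about 5.5 pre-period early neonatal deaths per arm (an assumption), and on independent women, equal SD and no attrition. Changing the pre-period length or the period covered by the 18 deaths moves them by a few points for the interaction and to at most about 45% for the pooled DiD effect, so the conclusion does not change. This is worth correcting before analysis, but it does not affect the primary analysis population.

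**What to change.** - **Section 2.12:** replace the 91% with the power of the planned DiD model, or label it as pooled post-period power that does not apply to that model. Labelling alone is not enough. Beside it, state the expected 95% CI half-width of the loss-type difference under the interaction form chosen.
- **Section 2.13:** say which lower-order loss-type terms enter the model, since this moves the half-width from about 4.4 to about 10 points. Describe the analysis as exploratory, as is done for EPDS ≥ 13, and report both the early-neonatal-death effect and the loss-type difference with 95% CIs.
- **Section 3.2:** base the statement about one protocol for all perinatal losses on those intervals, and say that neither a similar pooled estimate nor a non-significant interaction will be taken as sufficient.

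Cost: a few sentences, with no new data or participants. The downside is a less favourable stated figure and a softer policy claim.

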### Statistical analysis

2.13

The primary Difference-in-Differences (DiD) model will be specified as a linear regression with block fixed effects:$$EPDS=\beta_{0}+\beta_{1}(Arm)+\beta_{2}(Time)+\beta_{3}(Arm\times Time)+\gamma_{k}(Block_{k})+\epsilon$$where *Arm* (1 = intervention, 0 = control), *Time* (1 = post, 0 = pre), and the interaction term (*Arm* × *Time*) represents the DiD estimator (*β*₃). A negative *β*₃ will indicate a reduction in depressive symptoms attributable to C-COMPASS. Block fixed effects (*γ*_k_) will account for time-invariant block-level confounders, including baseline ASHA performance, population characteristics, and facility access.

The pre-specified secondary binary outcome (EPDS ≥ 13) will be analysed using a logistic DiD model with the same structure. SDS and BGQ scores will be analysed using linear DiD models with block fixed effects, while BGQ screen-positive (≥4) will be analysed using logistic DiD models. Implementation outcomes (visit completion, referral completion, and documentation completeness) will be reported as proportions with 95% confidence intervals.

Parallel trends will be assessed by comparing pre-intervention EPDS distributions across study arms and blocks, along with baseline sociodemographic characteristics (20). A maximum of one additional covariate beyond block fixed effects will be included, selected *a priori* (most likely gravida or previous stillbirth) (21). A pre-specified sensitivity analysis will replicate the primary model in an expanded population including early neonatal deaths, incorporating a perinatal loss type indicator and its interaction with the intervention effect. All analyses will be conducted using Stata version 16 or R version 4.4+.

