Several limitations must be acknowledged. The quasi-experimental DiD design, while appropriate given the operational constraints of embedding evaluation within a running programme, does not provide the causal certainty of a cluster-randomised trial. Block-level allocation is determined by programme implementation schedule rather than random assignment, and unmeasured time-varying confounders at block level, such as a community event, a local health programme, or seasonal migration patterns differentially affecting one block, cannot be fully excluded, even with block fixed effects. The pre-intervention period of approximately eight weeks is short, which limits formal statistical testing of the parallel trends' assumption; while the four-block design partially mitigates this, the concern cannot be eliminated. The primary sample of approximately 146 women is sufficient for the continuous EPDS primary outcome at 81% power but is underpowered for confirmatory testing of the binary EPDS ≥ 13 threshold, which should be interpreted as exploratory and directional. ASHAs in the intervention blocks are not blinded to the nature of the intervention, introducing the possibility of social desirability effects in self-reported implementation metrics, particularly visit completion and documentation completeness. The EPDS was originally validated for postnatal depression after live birth; while it has been used in stillbirth populations across multiple settings, its psychometric properties specifically in the context of perinatal grief in rural North India have not been formally validated, and cultural norms around mourning, including the social expectation that a bereaved woman will not laugh or plan for the future, may influence item-level responses in ways that are not fully separable from clinical depression. A residual risk of exclusion remains for women who experience stillbirth entirely outside facility or ASHA notification pathways, including those in the most geographically isolated, temporary migrants and women who relocate immediately after delivery. While the dual notification design and backup ANM pathway minimise this risk, penetration data collected during the study will allow estimation of the proportion of identifiable cases successfully enrolled, and any systematic differences between enrolled and non-enrolled women will be reported. Finally, the study is conducted in a single district in one state; while Palwal's epidemiological profile is broadly consistent with high-burden rural North Indian settings, immediate generalisability to other states and contexts should not be assumed.

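### The primary DiD model and the sample size make no allowance for block-specific change between periods; if ordinary standard errors are used and such change exists, the interval for β₃ is too narrow, and the stated 81% power is not the power of β₃

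*Protocol article*

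**What the plan says.** - **Model (Section 2.13).** "The primary Difference-in-Differences (DiD) model will be specified as a linear regression with block fixed effects". The displayed equation has arm, time, arm × time, block effects and a single error term; β₃, the arm × time coefficient, is the DiD estimator. The block effects "will account for time-invariant block-level confounders, including baseline ASHA performance, population characteristics, and facility access". No standard-error estimator is named.
- **Allocation (Sections 2.7 and 3.1).** Two blocks receive C-COMPASS and two are controls, chosen purposively and matched. "Block-level allocation is determined by programme implementation schedule rather than random assignment".
- **Sample size (Section 2.12).** For a 3.5-point difference, SD 6.5, two-sided 5% and 80% power, "a minimum of 55 women per arm in the post-intervention period is required"; 56 per arm is said to give about 81%. On the pre-period: "Over the 8-week pre-intervention period, approximately 17 women per arm are expected". The total is about 146. No intra-cluster correlation (ICC) or design effect appears.
- **Limitations (Section 3.1).** The article says it cannot fully exclude, even with block fixed effects, "unmeasured time-varying confounders at block level, such as a community event, a local health programme, or seasonal migration patterns differentially affecting one block". It still describes the sample as sufficient at 81% power.
- **Future work (Section 3.2).** It calls for "a fully powered cluster-randomised controlled trial with the administrative block as the unit of allocation and a pre-specified intra-cluster correlation coefficient".

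**The concern.** β₃ is the mean post-minus-pre change in two intervention blocks less the same quantity in two control blocks. Block fixed effects cancel whatever is constant within a block. They do not cancel a shift in one block between March–May and May–November. With two blocks per arm, half of any such shift passes straight into β₃, and a woman-level residual does not count it as uncertainty.

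The article names sources of such shifts, but treats them only as a caveat about causal interpretation and makes no allowance in the variance or the sample size. It reserves an ICC for the next trial.

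What is at stake is the reading of the primary result. Section 2.2 hypothesises significantly lower symptoms, Section 2.13 treats a negative β₃ as attributable to C-COMPASS, and Section 3.2 plans to carry a favourable result to state and then national bodies. Chance drift in one block could be reported as a programme effect. Separately, a reader who relies on 81% power would misjudge how much a null or a positive β₃ tells them.

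**Working it through.** **Inputs.** From Section 2.12: difference 3.5, SD 6.5, two-sided α 0.05, 17 pre and 56 post women per arm, two blocks per arm. Assumed, because the article gives no value: block-period ICC ρ from 0 to 0.10, where the block-by-period variance is τ² = ρ × 6.5².

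**1. The plan's own figures reproduce.**
- n per arm = 2 × (1.96 + 0.842)² × 6.5² / 3.5² = 54.2, rounded up to 55.
- SE with 56 per arm = 6.5 × √(2/56) = 1.23. Power = Φ(3.5/1.228 − 1.96) = Φ(0.89) = 81%.
- Total = 2 × (17 + 56) = 146.

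The 55 and the 81% are those of a two-sample comparison of independent women in the post period alone.

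**2. Power of β₃ with no clustering.** The DiD contrast also carries the sampling error of the pre-period:
- SE(β₃) = 6.5 × √(2/17 + 2/56) = 2.55.
- Power = Φ(3.5/2.545 − 1.96) = Φ(−0.585) = 28%.

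The Abstract and Section 2.4 give a pre-period of 10–12 weeks instead of 8. Twelve weeks at 9.2 women per arm per month is about 25 per arm. Then SE = 6.5 × √(2/25 + 2/56) = 2.21 and power = Φ(1.583 − 1.96) = 35%, so the conclusion is unchanged.

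**3. Adding block-by-period variation.** Each block's change contains two block-period deviations (variance 2τ²). Averaging two blocks gives τ² per arm, and differencing the arms gives 2τ². Hence

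Var(β₃) = (1 − ρ) × 6.5² × (2/17 + 2/56) + 2 × ρ × 6.5².

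At ρ = 0.02: 0.98 × 6.48 + 2 × 0.845 = 8.04, so SE = 2.835. Power with a normal critical value is Φ(3.5/2.835 − 1.96) = 23%.

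**4. Behaviour of the written model.** Data were simulated with no true effect: four blocks, 8 or 9 pre and 28 post women each, 20,000 runs per setting. The model was fitted with ordinary standard errors on 140 residual df. A t-test on the four block changes (2 df, critical value 4.30) was run alongside.

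| Assumed ρ | True SE of β₃ | False-positive rate, ordinary SE | Coverage of its 95% CI | Power, normal critical value and true SE | Power, 2 df | 95% half-width, 2 df |
|---|---|---|---|---|---|---|
| 0 | 2.55 | 5.0% | 95.0% | 27.9% | 13.4% | 10.95 |
| 0.01 | 2.69 | 6.6% | 93.4% | 25.4% | 12.5% | 11.59 |
| 0.02 | 2.83 | 7.8% | 92.2% | 23.4% | 11.8% | 12.20 |
| 0.05 | 3.22 | 12.8% | 87.2% | 19.1% | 10.3% | 13.86 |
| 0.10 | 3.78 | 20.2% | 79.8% | 15.1% | 8.9% | 16.26 |

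The false-positive rates and coverages are simulated; the other columns follow from the formula. The ordinary 95% half-width is about 1.96 × 2.545 = 4.99 points whatever ρ is. At ρ = 0.05 the model's mean SE was 2.49 against a true SD of 3.22. The block-level t-test held between 4.8% and 5.3% throughout.

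**The case against.** The strongest reply is that the article fixes a mean model, not a standard error. An analysis plan that is not shown could name another estimator, and nothing in Section 2.13 rules that out. This stands: independence in the analysis is inferred from the single error term and from Section 2.12, so the claim about the interval must be conditional. It does not rescue the sample size. Nor would a routine cluster-robust standard error settle the matter, because it is unreliable with four clusters.

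Second, a reader might infer that the interval is certainly too narrow. The documents do not support that. At zero block-by-period variance the ordinary test is correct, and no ICC is given. The relevant quantity is what remains after stable block differences are removed, within one district and in under a year. It may be small, and the 13% and 20% rates need values of 0.05 and 0.10 for which the article offers no evidence. Section 2.7 also matches on the absence of a co-occurring mental health programme, and Section 2.15 applies the same outcome assessment in all blocks. Against this, Section 3.1 itself says that block-specific shocks cannot be excluded.

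Third, other tempting arguments should not be used:
- Applying a design effect to the 81% describes a post-only comparison whose ICC would include stable block differences that the DiD removes.
- A permutation floor for the p-value has no randomisation to rest on and ignores the matched pairs.
- The arm term is redundant beside full block effects, but software drops it and β₃ is unchanged.

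Fourth, block-level inference on 2 df has very low power, and some analysts would prefer inference conditional on these four blocks. That is a fair reason to report the 2-df interval beside the model-based one and not as the only inference. Section 3.2 also ties escalation to feasibility and a clinically meaningful reduction, not to significance, which softens the policy risk without removing it.

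**Conclusion.** The concern holds in conditional form. The model and sample size as published make no allowance for block-by-period variation, with two non-randomised blocks per arm and an explicit concession that such variation is possible. If ordinary standard errors are used, the nominal 5% test has a true size of about 6 to 8% at an assumed ICC of 0.01 to 0.02, 13% at 0.05 and 20% at 0.10; at 0 it is correct.

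The power finding needs no ICC assumption. The 81% is not the power of the primary estimator, which is about 28% on the article's own SD, effect and numbers. With a normal critical value it is about 25%, 23% and 19% at ICC 0.01, 0.02 and 0.05. On 2 df it is about 9 to 13% over ICC 0 to 0.10. Four blocks can support an estimate with a candid interval, but not a confirmatory significance claim.

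**What to change.** In Section 2.13:
1. Keep β₃ as the point estimate.
2. Report the post-minus-pre change in mean EPDS for each of the four blocks, and an interval from those four changes using t with 2 df.
3. Report the model-based interval beside it, labelled as conditional on no block-by-period variation, and name its standard-error estimator.
4. State that four non-randomised blocks support estimation and not a confirmatory test, and align the hypothesis in Section 2.2 with that.

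In Section 2.12, the Abstract and Section 3.1, restate the 81% as the power of a post-period comparison of independent women, and give the power of β₃ with the ICC range assumed. The 91% for the expanded population in Section 2.12 has the same basis: with 74 per arm, Φ(3.5/(6.5 × √(2/74)) − 1.96) = 91%. It needs the same label.

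The work is wording and light programming, with no new data. The real cost is in what can be claimed: the half-width goes from about 5 EPDS points to about 11 or more, and a claim of conventional significance is given up. That changes the stated purpose of the primary analysis and should be acknowledged openly.
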